**Statistical analysis:**

*Phase I: Feasibility and toxicity.* Patients will receive concurrent treatment with extracranial radiosurgery and Sutent. Both the radiation dose and Sutent dose will be escalated as the trial progresses from Levels 1 through 5 as shown in Table 1. The starting radiation dose is 40 Gy in 10 fractions and the starting Sutent dose is 25 mg PO QD. The dose escalation strategy is as follows: The trial will start with dose level 1. At each level, 3 patients will be treated and their toxicities will be assessed. If no patients experience dose limiting toxicity, the trial will proceed to the next dose level. If 1 patient develops unexpected acute toxicity at any dose level, an additional 3 patients will be treated at that dose level. If ≥2 patients experience unexpected toxicity, the previous dose level will be declared the maximal tolerated dose for Phase II evaluation

*Phase II (Includes 3 to 6 patients from Phase I MTD):* The median progression free survival with optimal chemotherapy alone for the 4 most common tumor types (lung, breast, prostate and colorectal) ranges from 2.2 to 10.6 months, depending on primary tumor site and degree of pretreatment. Therefore, we will assume a median time to progression of 6.4 months (standard deviation 3.2 months) with chemotherapy alone. Using the data from this trial, response rates will be estimated and Kaplan-Meier curves generated for progression-free and overall survival (1). With 38 patients for the phase II portion, this study has 87% power (α=0.05) to detect a 25% increase in time to progression. Also the 2 year freedom from progression is <5% with chemotherapy therapy and this study has 70% power (α=0.05) to demonstrate a 10% absolute increase in 2 year progression-free survival.

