**Table 1. Phase I Dose Levels**

| **Dose Level** | **Radiation Dose** | **Sutent Dose** |
| --- | --- | --- |
| 1 | 40 Gy in 10 fractions | 25 mg PO QD |
| 2 | 40 Gy in 10 fractions | 37.5 mg PO QD |
| 3 | 50 Gy in 10 fractions | 37.5 mg PO QD |
| 4 | 50 Gy in 10 fractions | 50 mg PO QD |
| 5 | 60 Gy in 10 fractions | 50 mg PO QD |

.

Phase I dose escalation will proceed according to a “3+3” design. After 3 patients have been treated on each dose level, they will be followed for at least 30 days. If 0 of 3 patients have DLTs, the dose will be escalated to the next dose level. If ≥2 of 3 patients have DLTs, dose escalation will be terminated and the next lowest dose level will be declared the maximal tolerated dose for Phase II evaluation. If 1 of 3 patients has a DLT, then three more patients will be treated at the same dose level and if the incidence of DLT among six patients is < 2 of 6, the dose will be escalated to the next level for that site.

- Grades 3-5 non-hematological toxicities (excluding nausea, vomiting, and alopecia) and Grade 4-5 hematological toxicities will be referred to as dose limiting toxicities (DLT).
  - Esophagitis and mucositis are very common side effects with radiation therapy and grade 3 side effects can be seen after palliative courses of radiotherapy. Therefore, grade 3 mucositis or esophagitis lasting ≤ 7 days will **not** be considered a DLT. If the grade 3 mucositis or esophagitis lasts > 7 days, it will then be considered a DLT.
- The recommended phase II dose will be 1 dose level below the defined MTD or at the maximum tested dose if the MTD has not been reached.

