**12. TOXICITY**

- Radiation side effects are limited to the area involved in the treatment field(s). Acute and late toxicity related to radiation therapy include fatigue, nausea and vomiting, myelosuppression, skin erythema, subcutaneous fibrosis, esophagitis, pericarditis, diarrhea, cystitis, proctitis, myelitis, acute radiation pneumonitis, late pulmonary fibrosis, esophageal stricture, liver dysfunction, kidney damage, small bowel obstruction.
- Sutent toxicities are discussed in detail in Section 9.7
- Grade 3-5 non-hematological toxicities (excluding nausea, vomiting, and alopecia) and Grade 4-5 hematological toxicities will be referred to as dose limiting toxicities (DLT).
  - Esophagitis and mucositis are very common side effects with radiation therapy and grade 3 side effects can be seen after palliative courses of radiotherapy. Therefore, grade 3 mucositis or esophagitis lasting ≤ 7 days will not be considered a DLT. If the grade 3 mucositis or esophagitis lasts > 7 days, it will then be considered a DLT.
- All life-threatening Grade 4 and all fatal toxicities (Grade 5) must be reported immediately and evaluated.
- Acute toxicity: Acute side effects are considered as occurring ≤ 30 days from the start of radiation therapy. They will be documented using the NCI Common Terminology Criteria for Adverse Events (CTCAE) version 3.0 (A copy can be downloaded from [http://ctep.info.nih.gov](http://ctep.info.nih.gov/)).
- Late toxicity: Late side effects are considered occurring > 30 days from the start of radiation therapy. They will be evaluated and graded according to the RTOG Late Morbidity Scoring Scale (See Appendix).

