**16. STATISTICAL CONSIDERATIONS**

- Phase I: The primary objectives are to determine the maximum tolerated dose (MTD) and dose limiting toxicity (DLT) of extracranial stereotactic radiation therapy in combination with Sutent when given to all sites of involved disease in patients with metastatic cancer.
- For dose escalation purposes, the major endpoint will be dose-limiting toxicity occurring within 30 days after the start of radiation therapy.
- Dose limiting toxicity is defined as follows: Grade 3-5 non-hematological toxicities (excluding nausea, vomiting, and alopecia) and Grade 4-5 hematological toxicities.
  - Esophagitis and mucositis are very common side effects with radiation therapy and grade 3 side effects can be seen after palliative courses of radiotherapy. Therefore, grade 3 mucositis or esophagitis lasting ≤ 7 days will not be considered a DLT. If the grade 3 mucositis or esophagitis lasts > 7 days, it will then be considered a DLT.
- The MTD for a specific area will be exceeded if 2 or more patients out of 6 (or a third or more) with disease at that site experience DLT at that dose. The dose immediately below will be recommended for further study.
- Phase II: *(Includes 3 to 6 patients from Phase I MTD):* The median progression free survival with optimal chemotherapy alone for the 4 most common tumor types (lung, breast, prostate and colorectal) ranges from 2.2 to 10.6 months, depending on primary tumor site and degree of pretreatment. Therefore, we will assume a median time to progression of 6.4 months (standard deviation 3.2 months) with chemotherapy alone. With 38 patients, this study has 87% power (α=0.05) to detect a 25% increase in time to progression. Also the 2 year freedom from progression is <5% with chemotherapy therapy and this study has 70% power (α=0.05) to demonstrate a 10% absolute increase in 2 year progression-free survival.
  - All patients included in the study will be assessed for response to treatment, even if there are major protocol treatment deviations or if they are ineligible (intent-to-treat population). Criteria described in Section 10 will be used to assign each patient to one of the following response categories: 1) complete response, 2) partial response, 3) stable disease, 4) progressive disease, 5) early death from malignant disease, 6) early death from toxicity, 7) early death because of other cause, or 8) unknown (not assessable, insufficient data).

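### The phase I DLT definition excludes nausea and vomiting at every grade, so an isolated grade 4-5 event adds nothing to the 3+3 count

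*Protocol*

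**What the plan says.** Section 16 (Statistical Considerations, phase I) makes DLT within 30 days of the start of radiation the main endpoint for dose escalation and defines it as "Grade 3-5 non-hematological toxicities (excluding nausea, vomiting, and alopecia) and Grade 4-5 hematological toxicities". Section 10 (Phase I Dose Escalation Rules) and Section 12 (Toxicity) give the same definition with the same parenthesis. None of the three attaches a grade, duration or antiemetic condition to the exclusion.

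All three sections add a second exemption, and that one is limited: "Therefore, grade 3 mucositis or esophagitis lasting ≤ 7 days will not be considered a DLT". If the event lasts longer, it counts.

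Section 10 then applies a 3+3 rule:
- 0 of 3: "If 0 of 3 patients have DLTs, the dose will be escalated to the next dose level".
- 1 of 3: three more patients are treated at the same level, and escalation follows if fewer than 2 of 6 have a DLT.
- 2 or more of 3: escalation stops.

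The synopsis (Statistical analysis, phase I) words the rule differently. It says "If no patients experience dose limiting toxicity, the trial will proceed to the next dose level", but its expansion trigger reads "If 1 patient develops unexpected acute toxicity at any dose level, an additional 3 patients will be treated at that dose level".

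On reporting, Section 12 says "All life-threatening Grade 4 and all fatal toxicities (Grade 5) must be reported immediately and evaluated".

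**The concern.** The exclusion applies to the whole grade 3-5 class. Leaving out grade 3 nausea and vomiting is a common and defensible choice for a regimen in which both are known effects: Section 12 lists them for radiation and Section 9.7 for Sutent. Leaving out grades 4 and 5 is a different matter, because Section 12 itself treats those grades as life-threatening or fatal. The protocol gives no reason for extending the exclusion that far, whereas it explains the mucositis and esophagitis exemption and confines it to short grade 3 events.

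At stake is the dose decision after such an event. If it is the patient's only severe toxicity, the rule as written sends the next cohort to a higher dose of radiation or Sutent.

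**Working it through.** The protocol gives no figure to reproduce here. The point rests on the wording; the arithmetic only indicates its size.

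**The decision rule.** Take a cohort of three in which *k* patients have isolated grade 4-5 nausea or vomiting and nobody has another DLT.

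| k | Count as written | Decision | Count if grade 4-5 is included | Decision |
| --- | --- | --- | --- | --- |
| 1 | 0/3 | escalate | 1/3 | treat three more |
| 2 | 0/3 | escalate | 2/3 | stop |
| 3 | 0/3 | escalate | 3/3 | stop |

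**Does other text restore these events to the count?**
- Section 9.10 treats any drug-related grade 3 or 4 non-hematopoietic event as dose-limiting, with no exclusion for nausea or vomiting. Its heading limits it to phase II, so it does not govern escalation.
- The synopsis trigger carries no exclusion, but *unexpected* is undefined. Nausea and vomiting are listed as known effects, so such an event could be called expected. The same paragraph also moves to the next level when no patient has a DLT.
- Immediate reporting and evaluation (Section 12), review at the biweekly meetings (Section 15) and 24-hour reporting to the drug supplier (Section 15.1) are not tied to the DLT count. The monthly rate review in Appendix 3 is triggered by two or more of the same event in a month, or more than six in six months, so a single event does not trigger it.

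**Size per dose level.** With *p* the per-patient DLT probability, a level is cleared with probability

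P(clear) = (1 − p)³ + 3p(1 − p)²(1 − p)³ = (1 − p)³ + 3p(1 − p)⁵.

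Assumptions, none of them in the protocol: other DLTs occur in 10% of patients; grade 4-5 nausea or vomiting occurs in a proportion *q* of 1% or 2%; a share *d* of patients with such an event also have another counted DLT. Independence is d = 0.10.

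As written, p = 0.10: 0.729 + 3 × 0.10 × 0.59049 = 0.906.

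With grade 4-5 counted, p = 0.10 + q(1 − d). The last column is the chance that a first cohort reads 0/3 as written but at least 1/3 with the cap: 0.90³ − (1 − p)³.

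| q | d | p | P(clear) | Fall (points) | First cohort changed |
| --- | --- | --- | --- | --- | --- |
| 1% | 0.10 | 0.109 | 0.891 | 1.5 | 2.2% |
| 1% | 0.50 | 0.105 | 0.898 | 0.8 | 1.2% |
| 1% | 0.90 | 0.101 | 0.905 | 0.2 | 0.2% |
| 2% | 0.10 | 0.118 | 0.875 | 3.1 | 4.3% |
| 2% | 0.50 | 0.110 | 0.889 | 1.7 | 2.4% |
| 2% | 0.90 | 0.102 | 0.903 | 0.3 | 0.5% |

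Under independence, the fall is 1.0-2.2 points if the background DLT rate is 5% and 1.7-3.5 points if it is 20%.

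One counted event would not by itself end escalation. After one isolated event in three, the next three patients are all free of DLT with probability (1 − p)³, which is 0.69-0.73 over the table, and the level then clears at 1 of 6.

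**The case against.** The strongest reply is that the case hardly arises. Vomiting threatens life through dehydration, metabolic disturbance, aspiration or bleeding, and each of these at grade 3 or above is a non-hematological toxicity that the definition counts. What is left is a grade 4-5 event with no other severe toxicity recorded, which is largely a coding matter. On that view the independence rows overstate the effect. This stands: the 90% overlap rows are the more realistic ones, and the 3.1-point and 4.3% figures are upper ends of an assumed range.

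Second, grade 4-5 vomiting would ordinarily be called unexpected, so the synopsis trigger might catch it. That is a possible reading, and it means the outcome is not settled in every sentence of the protocol. But the trigger depends on an undefined term, and the body sections, which hold the full rule, do not use it.

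Third, the safeguards are substantial. Section 10 requires at least 30 days of follow-up after the three patients are treated, and Section 12 requires immediate evaluation. Under Appendix 3 the committee chair decides whether events reported by phone need immediate action, and its phase I tables call for a phone report to the FDA within 24 hours for grade 4-5 events. Escalation without any review is therefore not what the protocol describes. Even so, holding the dose would mean overriding the written rule by discretion; the count stays at 0 of 3.

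Last, the exclusion may be deliberate, since it appears three times and groups nausea and vomiting with alopecia. That supports the grade 3 exclusion. The protocol offers nothing to support it for grades 4 and 5.

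**Conclusion.** The point holds as a minor wording correction. The reading of the text does not depend on any assumed rate: Sections 10, 12 and 16 exclude nausea and vomiting at all grades, so an isolated grade 4-5 event leaves the count unchanged, and with no other DLT Section 10 escalates. The practical effect is small. With a 10% background DLT rate and 1-2% grade 4-5 nausea or vomiting, counting these events changes clearance of a level by a fraction of a point if nearly all of them bring another DLT, and by at most about 3 points if they are independent. No sample size, power figure or efficacy analysis depends on it.

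**What to change.** In Sections 10, 12 and 16, limit the exclusion to grade 3 nausea and vomiting and state that grade 4 or 5 nausea or vomiting is a DLT. Whether grade 3 should also carry a duration or antiemetic condition is for the sponsor to decide.

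In the synopsis, replace both references to unexpected toxicity with DLT, so that one definition drives every escalation statement. Make the two changes together: changing the synopsis alone would remove the only trigger that is free of the exclusion.

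The cost is an edit to three sections and the synopsis. No new data are needed, because adverse events are already assessed weekly during treatment and at each follow-up visit. The price is a slightly higher chance of expanding or stopping at a level: clearance is 0.2-3.1 points lower across the tabulated assumptions.

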Hypertension: Hypertension was noted in 15 to 28% of patients receiving Sutent vs. 11% for placebo. Grade 3 hypertension occurred in 4 to 6% of patients receiving Sutent vs. 0% for placebo. No case of grade 4 hypertension was reported. Careful monitoring and use of antihypertensive therapy is recommended. Sutent should be discontinued in cases of severe hypertension (defined as >200 mgHg systolic or >110 mgHg diastolic).

Adrenal: Adrenal toxicity was noted in rats and monkeys treated with Sutent but to date, there have been no cases of clinical adrenal insufficiency, adrenal necrosis or hemorrhage in human clinical trials. Nonetheless, patients receiving Sutent that experience stress such as surgery, trauma or severe infection should be monitored for adrenal insufficiency.

Gastrointestinal: Diarrhea, nausea, stomatitis, dyspepsia and vomiting were the most commonly reported gastrointestinal events occurring in patients who received Sutent. Diarrhea and stomatitis occurred more commonly in patients treated with Sutent than placebo. Supportive care for gastrointestinal adverse events, such as anti-nausea or anti-diarrheal medication should be prescribed as needed.

Skin: Skin discoloration, often to a yellowish hue occurred in approximately 1/3 of patients treated with Sutent. Depigmentation of the hair or skin, dryness, cracking, blistering or rash was also reported.

9.8 Potential Drug-Drug Interactions: SU11248 is mediated metabolized by the liver by CYP3A4. Therefore CYP3A4 inducers such as rifampin will result in a 56-79% reduction in SU11248 serum doses while CYP3A4 inhibitors such as ketoconazole will result in a 59-76% increase in SU11248 serum doses. For patients who are being concomitantly treated with a potent CYP3A4 inhibitor or CYP3A4 inducer, alternative treatments that lack potent CYP3A4-inducing properties should be considered. For patients who require treatment with a potent CYP3A4 inhibitor, a dose reduction should be considered in the presence of severe adverse events. For patients who require treatment with a potent CYP3A4 inducer, a dose increase should be considered.

However, in-vitro studies indicate that SU11248 does not induce or inhibit the major CYP450 enzymes including CYP3A4.

9.9 Administration: Sutent may be taken with or without food. The following schedule is recommended for the phase I and phase II studies:

| **REGISTER** | *Treatment* | *Days*  *1-7* | *8-12* | *13-14* | *15-19* | *20-28* | *29-42* |

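### The phase I escalation rule differs between sections on which patients are counted and on what kind of toxicity triggers action

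*Protocol*

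**What the plan says.** The escalation rule appears three times in the protocol.

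- **Synopsis, Statistical analysis.** Escalation depends on DLT: "If no patients experience dose limiting toxicity, the trial will proceed to the next dose level". Expansion depends on something else: "If 1 patient develops unexpected acute toxicity at any dose level, an additional 3 patients will be treated at that dose level". So does stopping: "If ≥2 patients experience unexpected toxicity, the previous dose level will be declared the maximal tolerated dose for Phase II evaluation". Neither grade nor 'unexpected' is defined there.
- **Section 10.** DLTs are graded and counted over everyone at the level. "If ≥2 of 3 patients have DLTs, dose escalation will be terminated" covers the first three patients, and "If 1 of 3 patients has a DLT, then three more patients will be treated at the same dose level" covers expansion. After six patients the text sets this condition and result: "the incidence of DLT among six patients is < 2 of 6, the dose will be escalated to the next level for that site". No action is written for 2 or more of 6.
- **Section 16.** It uses the same graded DLT definition. However, it sets the MTD for a specific area and regards it as passed when "2 or more patients out of 6 (or a third or more) with disease at that site experience DLT at that dose".

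There is a single ladder of five radiation/Sutent pairs, given to all involved sites. No section lists anatomical sites, site cohorts or a separate ladder per site.

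**The concern.** Two things that a dose-escalation rule must fix are not fixed: the denominator and the event.

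**Denominator.** Under Section 10, two DLTs among six patients do not clear the level, whatever sites are involved. Under Section 16, the same two patients count together only if they share a site. The protocol has no site-specific dose to escalate, so the site wording cannot be carried out as written.

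**Event.** Under Sections 10, 12 and 16 a DLT is defined by grade, with listed exclusions, and expectedness is not one of them. Under the synopsis, a DLT that is expected prevents escalation but triggers neither expansion nor stopping. The reverse also holds: an unexpected low-grade event would expand the cohort under the synopsis but not under Section 10.

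A third, minor matter is the parenthesis in Section 16 about a third or more. At six patients it equals 2 of 6. Read literally it also covers 1 of 3, where both Section 10 and the synopsis add three patients.

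MTD and DLT are the phase I primary objective, and the protocol says there are no clinical data on the combination. An error here exposes patients at the next level and carries into the phase II dose.

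**Working it through.** The protocol states no operating figure for the phase I rule, so there is nothing to reproduce. The contradiction follows from the text alone. The figures below show how much it could matter.

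**1. Who is counted**

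Assumptions: six patients at one level; two sites (lung, liver); exactly two DLTs, with all C(6,2) = 15 pairs of patients equally likely. A patient counts for every site where he or she has disease. The protocol gives no site mix, so all 28 mixes of lung-only, liver-only and both were considered.

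Example mix (2 lung-only, 2 liver-only, 2 both): each site has 4 patients. If one lung-only and one liver-only patient have a DLT, the pooled count is 2/6 (not cleared), but by site it is 1/4 and 1/4 (not exceeded). There are 2 × 2 = 4 such pairs, so 4/15 = 27% are missed. Every other pair puts two DLTs at one site.

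| Mix (lung-only, liver-only, both) | Missed, '2 or more' | Missed, 'a third or more' |
|---|---|---|
| 2, 2, 2 | 4/15 | 4/15 |
| 2, 1, 3 | 2/15 | 2/15 |
| 1, 1, 4 | 1/15 | 1/15 |
| 3, 3, 0 | 9/15 | 0/15 |

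Over all mixes the range is 0 to 9/15 = 60% on '2 or more', and 0 to 4/15 = 27% on 'a third or more'. On the second reading 24 of 28 mixes miss nothing. The four that do, counting the mirror image of (2, 1, 3), sum to 4 + 2 + 2 + 1 = 9 of 28 × 15 = 420 pairs, or 2%.

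The 27% is conditional on two DLTs in six. The chance that a 3+3 level reaches exactly 2/6 (one DLT in each group of three) is (3pq²)², with q = 1 − p. At assumed DLT rates of 10/20/30% this is 0.059/0.147/0.194. Multiplied by 4/15, the unconditional miss in the example mix is about 1.6/3.9/5.2%, if patients enter in random order with respect to site.

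Section 16's condition can also seldom be evaluated. If a share f of patients has disease at a site (assumed 0.25 to 0.75), the chance that all six do is f⁶ = 0.0002 to 0.18. A true site-by-site escalation over five levels would need 15 to 30 patients per site. For three sites (assumed, each patient counted once) that is 45 to 90, against 52 planned for the whole trial.

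**2. What triggers action**

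Input: Section 9.7 states that "Grade 3 hypertension occurred in 4 to 6% of patients receiving Sutent vs. 0% for placebo". Grade 3 hypertension is non-hematological and not among the exclusions, so it is a DLT. As a listed Sutent effect it would naturally be called expected. The chance of at least one such event is 1 − (1 − r)ⁿ:

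| n | r = 4% | r = 6% |
|---|---|---|
| 3 (one cohort) | 0.115 | 0.169 |
| 6 (three at each of the two 50 mg levels) | 0.217 | 0.310 |
| 15 (three at each of five levels) | 0.458 | 0.605 |

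This assumes that the quoted rate applies within the DLT window. The last row also assumes it at 25 and 37.5 mg, so read it as an upper figure.

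**3. The parenthesis, on its literal reading only**

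The chance of clearing a level under Section 10 is q³ + 3pq² × q³. If 1 of 3 already exceeded the MTD, it would be q³.

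| Assumed DLT rate p | Section 10 | Literal 'third' at n = 3 |
|---|---|---|
| 10% | 0.906 | 0.729 |
| 20% | 0.709 | 0.512 |
| 30% | 0.494 | 0.343 |

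**The case against.** The best reply is that Section 10 is the dedicated escalation section, gives a pooled 3+3 on graded DLTs, and permits escalation only below 2 of 6. Section 16 never says that a pooled 2/6 is acceptable. Read together, a pooled 2/6 should not escalate, and most investigators would apply it so. The word 'unexpected' occurs in one synopsis paragraph that itself starts from DLT, so it may be loose shorthand.

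That is probably the intent, but it does not settle the text. Section 10 states no action at 2 or more of 6. The only graded-DLT sentence that does so is the one in Section 16 with the site denominator. The synopsis stops at two patients, but on the undefined event. A stopping rule should not depend on guessing which section prevails.

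The objections to the size of the effect largely stand. The example mix is the worst case when 'a third or more' is applied, and the 60% arises only if that phrase is ignored. The hypertension figures give the chance that the gap is met, not the chance of a wrong decision. They borrow rates from GIST and renal cell trials with no stated time window. Site counting can also err toward stopping: one DLT among two patients with a given site is a half, although 1/6 pooled would clear. The parenthesis is probably only a gloss on 2 of 6.

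**Conclusion.** The concern holds. The three statements contradict one another on the unit counted and on the triggering event, and this needs no numerical assumption. If Section 16 is followed, between 0 and 27% of two-DLT outcomes in six patients go unflagged on the 'a third or more' reading, and between 0 and 60% on the '2 or more' reading, depending on an assumed two-site mix. If the synopsis is followed, an expected DLT leaves the cohort without a next step. For grade 3 hypertension alone, that situation has a 12-17% chance per cohort of three if the Section 9.7 rate applies within the DLT window. The parenthesis about a third is a minor point. Because this rule protects patients and determines the phase I primary result, it must be fixed, even though Section 10 probably shows what was meant.

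**What to change.** State one rule, in the same words, in the synopsis and Sections 10 and 16, counting graded DLTs over all patients treated at a dose level:

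- 0 of 3: escalate
- 1 of 3: treat three more at the same level
- at most 1 of 6: escalate
- 2 or more of 3, or 2 or more of 6: MTD exceeded, stop escalation

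Then make these edits:

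- Section 10: delete 'for that site'.
- Section 16: delete the references to a specific area and to disease at that site. Remove the parenthesis about a third or limit it to six patients.
- Synopsis: replace 'unexpected acute toxicity' and 'unexpected toxicity' with DLT as defined in Section 10.
- Report toxicity by anatomical site descriptively.

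The cost is protocol wording. No extra patients or procedures are needed.

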  - All patients who have met the eligibility criteria will be included in the main analysis of the response rate. Patients in response categories 4 – 8 will be considered as failing to respond to treatment (disease progression).
  - All individual lesions will also be recorded as CR, PR, SD, or PD.
  - Overall survival is the time from the date of first study treatment until death from any cause.

Overall survival and progression-free survival (PFS) will be calculated using the Kaplan-Meier (1958) estimator.(40) Median survival times and their associated 90% confidence intervals will be derived using the method described in Brookmeyer and Crowley (1982).(41)

The percentage of patients with complete responses and the percentage with complete or partial responses will be calculated and confidence intervals derived. The pattern of failures (local or distant) will be summarized. Adverse effects will also be tabulated by type and level of severity. Potential prognostic variables, such as number of lesion sites at baseline, will be examined by fitting Cox (1972) regression models for progression-free and overall survival times.(42) Given the sample size, only univariate analysis will be performed.

- Accrual Rate and Study Duration
  - The estimated accrual will depend on toxicity encountered, but we anticipate enrolling 50-65 patients.
  - We anticipate enrolling 1-3 patients per month.

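### The 87% power for a 25% longer time to progression rests on a normal-mean calculation with an unsourced SD; on a time-to-event basis, 38 patients give roughly 33–50% (two-sided) or 45–63% (one-sided)

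*Protocol*

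**What the plan says.** Section 16 (Statistical Considerations, Phase II) notes that published median PFS on chemotherapy "ranges from 2.2 to 10.6 months, depending on primary tumor site and degree of pretreatment". It then sets the reference: "we will assume a median time to progression of 6.4 months (standard deviation 3.2 months) with chemotherapy alone". From this it concludes: "With 38 patients, this study has 87% power (α=0.05) to detect a 25% increase in time to progression". The synopsis (Statistical analysis) makes the same claim: "With 38 patients for the phase II portion, this study has 87% power (α=0.05) to detect a 25% increase in time to progression". Neither place names a test or says whether alpha is one- or two-sided.

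The next sentence in both places makes a second claim for the same 38 patients. It puts 2-year freedom from progression on chemotherapy below 5% and gives 70% power for a 10-point absolute gain.

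Section 13 defines PFS as the time from registration to progression or death. For the analysis, section 16 specifies the Kaplan-Meier estimator, and for the median: "Median survival times and their associated 90% confidence intervals will be derived", by the Brookmeyer-Crowley method.

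**The concern.** The 87% needs a standard deviation, and only a calculation on a mean uses one. Progression times are usually right-skewed and may be censored, and no section plans to compare mean progression times. The 6.4 months is the midpoint of the quoted range, (2.2 + 10.6)/2. The 3.2 months is exactly half of that and has no source.

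PFS is a primary phase II endpoint, and this is the only power figure given for a 25% effect. A reader of the protocol would expect a true 25% gain to be missed about 13% of the time. If the real power is far lower, a result that fails to separate from 6.4 months could be misread as evidence against the regimen.

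**Working it through.** **Inputs from the protocol.** n = 38, single arm; alpha 0.05; reference median 6.4 months; SD 3.2 months; 25% increase, so 6.4 × 1.25 = 8.0 months; 2-year freedom from progression below 5%.

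**1. The stated figure.** Standardised effect (8.0 − 6.4)/3.2 = 0.5. Signal 0.5 × √38 = 3.082. Two-sided power Φ(3.082 − 1.960) = 86.9%. Other readings miss 87%: one-sided z 92.5%; t-test 85.1% (two-sided) or 91.6% (one-sided); two-sample comparisons, two-sided, 34% (19 + 19) or 59% (38 + 38). So the 87% is a two-sided one-sample z-test with the median used as the mean.

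**2. That model against the next sentence.** Normal(6.4, 3.2) gives P(T > 24) = Φ(−5.5) ≈ 2 × 10⁻⁸. With mean 8.0 it is Φ(−5.0) ≈ 3 × 10⁻⁷. The 70% claim reproduces with 5% against 15%: rejecting at 5 or more of 38 progression-free has exact alpha 4.0% and power 69.3%. A null near zero does not give 70%: one success would then suffice to reject, and power against 10% would be 1 − 0.9³⁸ = 98%. The two adjacent statements therefore use incompatible distributions for one endpoint.

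**3. Power on a time-to-event basis.** Assumptions not in the protocol: all 38 patients have events (favourable to the plan), 6.4 months is a fixed reference, and PFS is Weibull with the same shape k under both medians. Solving for S(24) = p gives k = ln[ln(1/p)/ln 2] / ln(24/6.4). Power ≈ Φ(√38 × k × ln 1.25 − z), with √38 × ln 1.25 = 1.376 and z = 1.960 (two-sided 5%) or 1.645 (one-sided 5%).

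| Progression-free at 2 years, reference | k | Signal | Two-sided 5% | One-sided 5% |
|---|---|---|---|---|
| 7.4% (exponential) | 1.00 | 1.376 | 28% | 39% |
| 5% | 1.107 | 1.523 | 33% | 45% |
| 3% | 1.227 | 1.687 | 39% | 52% |
| 1% | 1.433 | 1.971 | 50% | 63% |

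The exponential row depends somewhat on the test: 26%/37% by a simulated one-sample log-rank test and 31%/42% by the exact chi-square test, so about 26–31% two-sided and 37–42% one-sided. It breaches the protocol's own ceiling of 5%, so it is a lower reference and not the main result.

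**4. The planned median interval.** With no censoring, the lower 90% Brookmeyer-Crowley limit exceeds 6.4 months when at least 24 of 38 patients are progression-free at 6.4 months: (24/38 − 0.5)/√[(24/38)(14/38)/38] = 1.68 > 1.645, while 23 of 38 gives 1.33. With a true median of 8.0, S(6.4) = 0.5^(0.8^k). This is 0.574 (exponential), 0.582 (5% at 2 years) and 0.604 (1%). The binomial probability of 24 or more is then 29%, 33% and 43%.

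**5. What 38 events can detect.** The median ratio for 80% power is exp[(z + 0.842)/(√38 × k)]. At k = 1.107 this is exp(2.802/6.826) = 1.51 two-sided and exp(2.487/6.826) = 1.44 one-sided, an increase of 44–51%. Under the exponential it is 50–58%.

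**The case against.** The strongest reply is that the calculation is right for its inputs, and that an SD of 3.2 with a median of 6.4 is possible. Both are true. A Weibull with shape 2.21 has that median and SD and would give 86% two-sided power; a lognormal would give 89%. A reader might infer that such an SD cannot occur, or that the protocol made an arithmetic slip. Neither follows. The difficulty is that these distributions leave 0.0003% (Weibull) or 0.1% (lognormal) progression-free at 2 years, against the roughly 5% behind the 70% statement.

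It can also be said that a rate near zero satisfies a bound of below 5%, and that a treatment described as potentially curative could produce a plateau the reference group lacks. The first is literally correct, and the second means that the 10-point target alone proves nothing about the reference distribution. What remains is that the 70% figure does not reproduce with a null near zero.

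Finally, section 16 plans estimation and names no test of PFS against 6.4 months; an analysis plan not shown may name one. This stands. The percentages in step 3 belong to a one-sample comparison assumed here, not to a test the protocol specifies. Only step 4 concerns the interval it does specify. But the 87% and the SD are printed in the protocol as a claim, so this is a misstatement there and not a detail left for later.

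**Conclusion.** The point holds as an error of method and assumption. The 87% does not describe the planned kind of analysis and conflicts with the 2-year baseline used beside it. With 38 events, a fixed reference of 6.4 months and Weibull PFS with 5% to 1% progression-free at 2 years, power is about 33–50% two-sided or 45–63% one-sided. Fewer events would lower it.

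Two stronger conclusions are not supported. A reader might infer that the 38 patients have no other justification; the 70% statement for 2-year PFS is a second one, and it reproduces at 69.3%. A reader might also infer that a true 25% gain would be missed more often than found. That is so for a one-sided test at 5% progression-free (45%), but not at about 3% or lower (52% at 3%), which the protocol's bound allows.

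**What to change.** Keep 38 patients. In section 16 and the synopsis, delete the SD of 3.2 months and restate the power on a time-to-event basis, giving the distribution, the number of events and the sidedness. Possible wording: *With 38 events, and assuming Weibull PFS with median 6.4 months and 5% progression-free at 2 years, power for a 25% increase in median PFS is about 33% (two-sided 5%) or 45% (one-sided 5%); 80% power needs an increase of about 44–51%.* The sponsor may prefer another distribution, provided it agrees with the 2-year rate used in the next sentence.

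The cost is protocol wording only: no extra patients and no change in treatment or follow-up. The stated power becomes much less favourable.
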